#### Inclusion criteria

Patients who will be recruited in this study should meet the inclusion criteria including:

(1) aged between 18 and 70 years

(2) not be taking part in any other clinical trials

(3) having no previous experience of catgut implantation at acupoints

(4) provide written informed consent

(5) presenting with typical symptoms of AR, such as rhinorrhoa, sneezing, nasal obstruction, and pruritus. These symptoms should last >1 h on most days. Some patients may have ocular symptoms due to outdoor allergens

(6) with positive skin prick tests performed by trained health professionals

A standardized vaccine (Alutard SQ, ALK- Abelló, Denmark) will be used in the prick test. Oral H1-antihistamines are not permitted before skin test. Skin prick tests should be read at the peak of their reaction by measuring the wheal and the flare approximately 15 min after the performance of the test.

#### Exclusion criteria

Patients with any of the following conditions will be excluded:

(1) pregnant women or women who have been trying to get pregnant in the last 6 months, or women who are lactating

(2) patients who are receiving immune therapy

(3) patients with other allergic diseases, such as bronchial asthma or allergic purpura

(4) patients with nasal polyposis

(5) heterologous protein allergy

(6) patients with other organic disorders, such as AIDS, vascular malformation, hypertension, hematologic diseases, diabetes mellitus, malignant tumor, and mental disorders

#### Withdrawal from the study

Study patients will be allowed or be asked to withdraw from the study if:

(1) they have been included in the trial but would not subject to the assigned treatment for varies reasons at any of the stages of the trial

(2) severe adverse events occur that necessitate withdraw of patients from the trial

(3) they do not fully participate in treatment or follow-up

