**Methods and design:**

This study compares real *versus* sham catgut implantation at acupoints in 242 patients with a history of PER or IAR and with a positive skin prick test (SPT). The trial will be conducted in the Teaching Hospital of Chengdu University of Traditional Chinese Medicine. In the study, patients will be randomly assigned by computer-generated randomization list into two groups and assessed prior to treatment. Then, they will receive two sessions of treatments (once per 2 weeks) for 4 consecutive weeks and have a follow-up phase of 12 weeks. The administration of catgut implantation (or sham-control) at acupoints follows the guidelines for clinical research on acupuncture (WHO Regional Publication, Western Pacific Series No.15, 1995), and is performed double-blindly by a well-trained physician in acupuncture. The main outcome measures include the primary and secondary indicators. Primary indicators are subjective symptoms scores evaluated by visual analogue scales (VAS) and Rhinoconjunctivitis Quality of Life Questionnaires (RQLQ). The secondary indicators are the results of laboratory examinations, such as serum allergen-specific IgE, nasal inflammatory cells counts (mast cells, eosinophils, and T cells) and nitric oxide concentration in nasal excretion. The use of anti-allergic medication will also be recorded as one of the secondary indicators. Furthermore, adverse events will be recorded and analyzed. If any participants withdraw from the trial, intention-to-treat analysis (ITT) and per-protocol (PP) analysis will be performed.

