### Outcome measurements

#### Primary outcome

The primary outcome measures will be the severity of the AR symptoms assessed by (VAS) [9] and the RQLQ [10,11]. In VAS, the severity of the combination of the nasal symptoms will be subjectively rated by the study patients on the scale. The severity of symptoms can be divided into mild, moderate, or severe based on the total severity VAS score (0 to 10 cm: mild, VAS 0–3; moderate, VAS 3.1-7; severe, VAS 7.1-10). VAS scores will be recorded every 2 weeks during the whole trial. Influence of AR on QOL will be measured by questionnaire every 4 weeks: at baseline, at the end of treatment, during the follow-up period, and at the end of follow-up period (a total of five times). Both the scores of VAS and RQLQ questionnaire will be blindly assessed.

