### Quality control

All acupuncturists are required to receive special training, including the technique for catgut implantation and the way to deal with adverse events. The acupuncturists should also learn how to use the randomization method in order to communicate with patients and to keep them blind to the treatment throughout the trial. Only those who have completed the required training and have passed all necessary examinations will be recruited for this trial. In order to maintain quality of this trial, all outcome assessments will be blinded. In addition, all researchers must understand the purpose and design of this trial. Audits will be conducted regularly on compliance with standard operation procedures every week. Report of audits should be presented to the chief monitor. If patients withdraw from the trial either in the treatment period or in the follow-up phase, the reason should be clarified and the rate should be analyzed in statistics.

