### Statistical analysis

In our preliminary study to compare the efficacy of catgut implantation at acupoints with intranasal glucocorticoid, it was suggested that efficiency was 93.75% in the catgut implantation group and 96.88% in the control group. In this study, we anticipate an improvement of no less than 15% after real catgut implantation at acupoints. However, there are no previous data regarding the VAS or RQLQ scores for the treatment of AR with catgut implantation at acupoints. Considering participants recruited in the two groups are in a 1:1 ratio, the following formula was used to estimate sample size [13]:

$$n_{1}=n_{2}={\left[\frac{Z_{\alpha }\sqrt{2\pi_{c}\left(1-\pi_{c}\right)}+Z_{\beta }\sqrt{\pi_{1}\left(1-\pi_{1}\right)+\pi_{2}\left(1-\pi_{2}\right)}}{\pi_{1}-\pi_{2}}\right]}^{2}$$

In the formula: n1, n2 represents the sample size of each group. π1, π2 is the overall rate of each sample, respectively. πc = (π1 + π2)/2, α = 0.05, Z_0.05_ = 1,96,β = 0.10,Z_0.10_ = 1.282. Statistical analysis will be performed using a 5% significance and 90% power, resulting in an estimated 121 patients per group.

To test our hypothesis, the first step is to assess the baseline characteristics of two groups using an unpaired *t* test or *x*^2^ testes. The second step is to compare the efficacy of real catgut implantation with the sham one, including the primary and secondary outcomes using two-sample t test. If there is any case lost in follow-up phase or withdrawn from the trial, the causes of withdrawal should be clarified. The intention-to-treat analysis (ITT) and per-protocol (PP) analysis should be conducted to test whether the result of this trial is credible. For relief medication, within-group as well as between-group comparisons of scores are to be made. Data will be analyzed using the Statistical Package for the Social Sciences software, version 15.0 for Windows (SPSS Inc., Chicago, IL, USA). Data are presented as mean and 95% confidence intervals (CI). The statistical analysis will be performed in a blinded manner by qualified statisticians.

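### Non-adherent patients may be asked to leave the study itself, with no provision for collecting later outcomes, which works against the planned intention-to-treat analysis

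*Protocol article*

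**What the plan says.** The section on withdrawal in the protocol article opens with "Study patients will be allowed or be asked to withdraw from the study if" and lists three grounds. Item (1) covers patients who, once included, do not take the treatment assigned to them, whatever the reason and whenever it happens. Item (2) concerns severe adverse events. Item (3) applies if "they do not fully participate in treatment or follow-up". The heading and the opening sentence both refer to the study, and nothing in the section distinguishes ending treatment from ending participation.

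On what follows a withdrawal, the section on quality control asks that "the reason should be clarified and the rate should be analyzed in statistics". The section on statistical analysis likewise says "If there is any case lost in follow-up phase or withdrawn from the trial, the causes of withdrawal should be clarified". Neither mentions further outcome measurement.

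On the analysis, the abstract says "If any participants withdraw from the trial, intention-to-treat analysis (ITT) and per-protocol (PP) analysis will be performed". The section on statistical analysis says "The intention-to-treat analysis (ITT) and per-protocol (PP) analysis should be conducted to test whether the result of this trial is credible". The primary outcomes are VAS and RQLQ. For the first, "VAS scores will be recorded every 2 weeks during the whole trial"; the second is completed every 4 weeks, five times in all.

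**The concern.** An ITT analysis compares all randomised patients as randomised, so it needs outcomes from those who missed a session or refused the assigned treatment. Items (1) and (3) single out the same patients as candidates for leaving the study. With no rule for continued collection, non-adherence can become missing outcome data through the protocol's own procedure.

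Patients who stop may be those with no benefit or with local reactions. The retained catgut is the only planned difference between the arms, so the reasons for stopping could differ by arm. If they do, the comparison of the remaining patients is biased, and a larger sample would not correct it. The late outcomes matter here because the pilot's reported advantage was in recurrence at 3 months of follow-up.

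**Working it through.** **1. What a removed patient would still contribute.** Treatment lasts 4 weeks and follow-up 12, so outcomes run to week 16 after randomisation. At the stated intervals this gives 16/2 = 8 VAS readings after baseline and 5 − 1 = 4 RQLQ readings after baseline, the first at week 4. Take the second session as due at week 2, which the two-weekly spacing implies. A patient who misses it and is asked to leave then would have the baseline values and at most one later VAS reading, and no RQLQ after baseline.

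**2. The plan's own sample size.** The article gives 121 per group from a two-proportion formula with Z values 1.96 and 1.282, but does not print π1 and π2. Reading the anticipated 15% as relative to the pilot's 93.75% gives π1 = 0.9375, π2 = 0.9375 × 0.85 = 0.7969 and πc = 0.8672:

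n = [(1.96 × √0.2303 + 1.282 × √0.2205) / 0.1406]² = 120.3, rounded up to 121.

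This reading contains no allowance for dropout. Reading the 15% as absolute (0.9375 versus 0.7875) gives 108.7, and 108.7 / 0.9 = 120.8, which also rounds up to 121. The document therefore does not show whether losses were allowed for. The point below does not depend on which reading is right.

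**3. Detectable difference for a continuous outcome.** The primary outcomes are scores compared by t test. In SD units, with 121 per arm, two-sided 5% and 90% power:

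(1.96 + 1.282) × √(2/121) = 3.242 × 0.1286 = 0.42 SD.

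If 10% are lost, 121 × 0.9 = 108.9 remain per arm, and 3.242 × √(2/108.9) = 0.44 SD.

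**4. Shift from selective removal (assumptions).** The documents give no withdrawal rate, so the rates here are assumed. If the worst-scoring fraction q of a normally distributed outcome is removed from an arm, the mean of those remaining moves by φ(z₁₋q)/(1 − q) SD. If removal correlates only ρ with the outcome, this is multiplied by ρ.

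- q = 0.05: 0.109
- q = 0.10: 0.195
- q = 0.15: 0.274

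| Removed, one arm vs the other | Shift, ρ = 1 | Shift, ρ = 0.5 | Share of 0.42 SD |
|---|---|---|---|
| 15% vs 5% | 0.274 − 0.109 = 0.17 (0.166 unrounded) | 0.08 | 40% / 20% |
| 10% vs 5% | 0.195 − 0.109 = 0.09 | 0.04 | 21% / 10% |
| Same fraction and same ρ | 0 | 0 | 0 |

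The arm that loses more of its worst scorers looks better than it is, so the bias can go either way. These figures treat removed patients as contributing nothing to the comparison, which is the least favourable handling.

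**The case against.** A reader might infer that every non-completer must be removed, that their data are discarded, and that the ITT analysis thereby becomes an analysis of completers. The documents do not support this. The wording is allowed or asked, so removal is optional and the clause also covers patients who leave by choice. Nothing says that recorded values are deleted or that a randomised patient drops out of the ITT set. Early VAS readings may exist, and how partial data are used is commonly left to an analysis plan. A patient who stops attending follow-up supplies no data whatever the rule says, so that half of item (3) is partly descriptive. The article is also condensed, and a fuller protocol might provide for continued collection.

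A reader might also object that ITT is run only if someone withdraws. This has little consequence. Withdrawal or loss triggers it, and without withdrawal, loss or non-adherence the ITT and per-protocol sets largely coincide. Which of the two decides the trial can properly be settled in an analysis plan.

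The 0.17 SD figure is close to a worst case: it needs complete removal of the worst tail and a threefold difference between arms. With blinded patients and identical needling, nothing in the documents predicts such a gap.

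These objections limit the size and certainty of the point. They do not remove it, because the withdrawal rule is printed in the article and refers to the study. If it is applied as written, no later analysis plan can recover outcomes that were never collected.

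**Conclusion.** The point stands as a defect in the withdrawal rule. It permits the investigators to end study participation for non-adherence and provides for no outcome collection afterwards, while the analysis section promises ITT. What may be lost is later VAS and RQLQ data from non-adherent patients. That loss is inferred from leaving the study combined with the absence of any continuation rule; it is not stated outright.

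The size of any bias is unknown. Under the assumed range it is about 0.04 to 0.17 SD against a detectable 0.42 SD, and zero if both arms lose the same fraction selected in the same way. The loss of precision alone is small, 0.42 to 0.44 SD at an assumed 10% loss. This should be fixed, but on the documents it does not make the trial's result invalid. The missing ranking of ITT and per-protocol is secondary.

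**What to change.** In the withdrawal section, separate two events: stopping the assigned treatment and leaving the study. Remove items (1) and (3) as grounds for being asked to leave the study. State that VAS, RQLQ, diaries and adverse events continue to be collected at the scheduled visits, to week 16, from all randomised patients unless consent is withdrawn. Record the date of and reason for stopping treatment by arm, in line with what the quality control section already asks. The clinical decision to stop treatment, including item (2), is not affected by this change.

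As a secondary change, state in the analysis section that ITT (all randomised, as randomised) is the primary analysis in every case and that per-protocol is supportive.

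The cost is a wording amendment and some effort to follow non-adherent patients at visits already scheduled. Some of them will still decline or fail to attend, so missing data will be reduced but not eliminated.

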### Recruitment

#### Hospital recruiting

In China, most of the patients with symptoms of AR will present at the otorhinolaryngology clinics. It is advisable that all physicians in our department should be familiar with the study inclusion and exclusion criteria and refer the appropriate patients to the PI or study physicians. Then the screening evaluations will be conducted and the information of the patients will be recorded. Patients who satisfy the inclusion criteria and are willing to participate in the trial will sign on the written informed consent. Then they will be randomized into either of the study groups and introduced to the acupuncturists.

#### Advertisements

Television and newspaper advertisements will be on display. Printed recruitment posters will also be pasted in the hospital and the university campus.

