## Methods and design

### Study design

This study will be a double-blind, randomized, sham-controlled trial conducted in the Department of Otorhinolaryngology-head and neck surgery, Teaching Hospital of Chengdu University of T.C.M., China. This study includes the following time points: a run-in period of 4 weeks after screening, a treatment period of 4 weeks, and a follow-up period of 12 weeks. The total study period will be 20 weeks. At the screening visit, medical history especially in relation to AR and other allergic diseases will be asked and recorded by a study physician based on a systemically designed questionnaire. Patients who satisfy the inclusion criteria will be recruited into the run-in period. After randomization, patients will be blindly assigned to either the real catgut implantation at the acupoints group or the sham group (controls). All patients will receive two treatments over a period of 4 weeks. Chlorphenyramine will be used as a rescue medication if the patients present with untolerable AR symptoms. At the same time, patients should complete visual analogue scales (VAS) [9] and Rhinoconjunctivitis Quality of Life Questionnaires (RQLQ) [10,11] before randomization, at the end of treatment, during and after the follow-up period, respectively. Meanwhile, inflammatory cells and mediators in nasal secretions will also be measured at these three visits. Outcome measurements will be assessed by evaluating the efficacy and safety of catgut implantation at acupoints in the treatment of AR.

The design of this study followed the guidelines of the Helsinki Declaration (Version Edinburgh 2000) and was approved by Sichuan Regional Ethics Review Committee on Traditional Chinese Medicine (TCM). Informed consent are to be obtained from all the study patients. Before signing the consent, all patients will be given enough time to decide whether to participate in the trial. Other treatment options instead of catgut implantation at acupoints will be available for those who are unwilling to be recruited in the study.

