#### Sham-controlled group

In the control group, the same acupoints are to be punctured with the same acupuncture needles and same length and angle according to standard techniques. The only difference between these two groups is that catgut would not be embedded into the acupoints in the sham-controlled group. Because of mild swollen tissue at acupoints immediately after puncture and lack of previous experiences for this therapy, the patients will not know whether catgut has been embedded into the acupoints. To ensure the blinding manner, acupuncturists are instructed not to communicate with the participants of whole treatment procedures.

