#### Standard protocol for catgut implantation at acupoints

Only pre-sterilized disposable needles (9#, Hanjiang Guoxiang Medical Appliance Factory, Yangzhou, China) and catguts (000, Pudong Jinhuan Medical Products Co. Lit, Shanghai, China)are used in the trial. For Yintang (EX-HN3), the needle is to be inserted with a depth of 1.0 cm, downward to the nose in a horizontal direction with respect to the shin. For Yingxiang (IL20), the penetration is 2.0 cm, in an oblique direction along the nasolabial sulcus towards the root of nose with respect to the skin. For Hegu, Zusanli, and Quchi, the penetration is 2.5 cm, in perpendicular direction with respect to the skin (Table 1). Twirling, lifting, and thrusting of the needle do not need to be performed. Both groups will receive one session of catgut implantation every 2 weeks for 4 weeks. Subjects will be advised to lie on a supine position. Pulse rate, blood pressure, and oxygen saturation are to be monitored routinely during the procedure as a precautionary measure. In both groups, pre-injection swabs with 75% alcohol and dry sterile cotton wool are to be used when withdrawing the needles. Before the puncture, it is advised to inject 0.5% Lidocaine of about 0.2 to 0.4 mL for each acupoint to alleviate the pain caused by inserting the needle. After treatment, the skin of the acupoints is prohibited to touch water or any cosmetics for 3 days.

**Table 1 T1:** Acupoints and manipulation for both real and sham catgut implantation group

**Time**	**Acupoints**	**Angle and direction**	**Depth ****(cm)**
First week of treatment	Yintang(EX-HN3)(unilateral)	Downward to the nose in a horizontal direction with respect to the shin	1.0
	Yingxiang(LI20)(both)	In an oblique direction along the nasolabial sulcus towards the root of nose with respect to the skin	2.0
	Hegu(LI4)(both)	In perpendicular direction with respect to the skin	2.5
Second week of treatment	Zusanli(ST36)	In perpendicular direction with respect to the skin	2.5
	Quchi(IL11) (both)	In perpendicular direction with respect to the skin	2.5

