The needle used for catgut implantation is similar to a kind of trocar. It is made up of two parts: the internal stylet and the external cannula with sharp pinhead which assures the cannula could puncture into the skin (Figure 3). In real catgut embedding, the internal stylet should be withdrawn from the cannula for about 1.5 cm at first. Then a catgut with the length of 2 to 3 mm will be put into the cannula from the side of pinhead. When the needle has been inserted into the acupoints with the correct depth, the catgut will be pushed into the tissue of the acupoint by the stylet. For the control group, the whole therapeutic procedure is the same as the real group except that the catgut is not present in the cannula. Patients in the control group will receive only the stimulus of needling but not of the catgut implantation.

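### Patient blinding relies partly on inexperience of the therapy, but inclusion criterion 3 does not clearly exclude people taught or trained in it, whom the campus posters can reach

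*Protocol article*

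**What the plan says.** **Recruitment.** Patients come by referral within the otorhinolaryngology department, through television and newspaper advertisements, and through posters: "Printed recruitment posters will also be pasted in the hospital and the university campus" (Advertisements). The campus is not named. The Study design section places the trial in the "Teaching Hospital of Chengdu University of T.C.M., China", so the natural reading is the campus of that TCM university.

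**Eligibility.** Inclusion criterion 3 is "having no previous experience of catgut implantation at acupoints". The six exclusion criteria are medical; the last, for example, is "patients with other organic disorders, such as AIDS, vascular malformation, hypertension, hematologic diseases, diabetes mellitus, malignant tumor, and mental disorders". None mentions TCM training, acupuncture practice, students or staff.

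**Basis of patient blinding.** The Sham-controlled group section gives two reasons why patients cannot tell their arm: mild swelling just after the puncture, and "lack of previous experiences for this therapy, the patients will not know whether catgut has been embedded into the acupoints". Acupuncturists are also told not to communicate with participants.

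**Difference between arms.** For controls, "the whole therapeutic procedure is the same as the real group except that the catgut is not present in the cannula" (Standard protocol for catgut implantation at acupoints).

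**Outcomes.** VAS and RQLQ are the primary outcomes, and both are completed by the patient (Primary outcome).

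**The concern.** The blinding argument assumes patients who do not know the therapy. A TCM campus plausibly holds people who have been taught acupuncture techniques or have watched them, and the posters invite them. If criterion 3 does not keep them out, the trial may enrol the very people for whom that assumption is weakest. They may also be more likely to hold a prior belief in the treatment.

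Because the primary outcomes are self-rated, they count as blindly assessed only if the patient is blind. A patient who guesses the arm correctly, and whose rating shifts as a result, adds to the difference between real and sham treatment something that is not an effect of the catgut.

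**Working it through.** No figure in the article depends on this point, so the check is mainly a comparison of passages.

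1. **What blinding needs.** There are two stated grounds. By its own wording, the swelling ground concerns the time immediately after puncture. VAS is recorded every 2 weeks throughout the trial, which includes 12 weeks of follow-up. For much of that period inexperience is the main stated ground still standing.

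2. **What criterion 3 secures.** It can be read in three steps:
   - Having received the treatment: covered.
   - Having performed it: arguably covered, since a practitioner has experience of it.
   - Having studied it, watched it or trained in acupuncture generally: not clearly covered.

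   The exclusion criteria do not fill the gap.

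3. **What the recruitment route adds.** Campus posters reach the third group. They are one route among several, and the article does not say how many patients they are expected to supply.

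4. **What a trained participant could notice.** Points, needle, length, angle and procedure are the same in both arms, so the handling and the stylet push give no cue on the protocol's wording. Pain from the puncture is dulled in both arms: "it is advised to inject 0.5% Lidocaine of about 0.2 to 0.4 mL for each acupoint to alleviate the pain". One step does differ: "Then a catgut with the length of 2 to 3 mm will be put into the cannula from the side of pinhead". The article does not say whether this loading is done out of the patient's sight. Someone who knows the technique would know to look for it, but nothing in the text shows that they could see it.

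5. **Sample size, for reference.** The stated 121 per group comes out of the printed formula if the 15% is read as relative to 93.75%. Then π1 = 0.9375, π2 = 0.85 × 0.9375 = 0.7969, Zα = 1.96 and Zβ = 1.282, giving n = 120.3, rounded up to 121. The point raised here does not alter that figure.

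6. **Sensitivity, on assumed inputs only.** Suppose a share s of each arm recognises its treatment, and this opens a real-minus-sham gap of 0.5 SD among them. Neither value comes from the article. The bias is s × 0.5 SD. With 121 per arm, SE = √(2/121) = 0.1286 SD. Two-sided rejection when there is no true effect is P(Z > 1.96 − bias/SE) + P(Z < −1.96 − bias/SE).

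| s (assumed) | Patients of 242 | Bias (SD) | Bias/SE | Rejection under the null |
|---|---|---|---|---|
| 0% | 0 | 0 | 0 | 5.0% |
| 10% | about 24 | 0.05 | 0.389 | 0.0581 + 0.0094 = 6.7% |
| 20% | about 48 | 0.10 | 0.778 | 0.1186 + 0.0031 = 12.2% |

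The table shows how a given degree of unblinding would translate into error. It does not estimate what will happen in this trial.

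**The case against.** The strongest reply is that the procedures are well matched. The sham uses the same points, needle, depth and angle, local anaesthetic is advised, and the thread is only 2 to 3 mm long. Nothing in the article says that a trained person could tell the arms apart. That stands. A reader might infer that TCM students and staff will recognise their arm; the document does not support this, and the one open cue, visible loading of the thread, would not be confined to them.

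A reader might also take criterion 3 to screen only for having been treated. The wording is wider than that, because it can cover having performed the technique. What remains open is knowledge gained by teaching, observation or general acupuncture training.

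Nor is inexperience the only support for blinding. Swelling is named beside it, and the matched procedure and the silence of the acupuncturists add to it.

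It is also fair to say that catgut implantation is not shown to be common knowledge on the campus: even the trial's acupuncturists receive special training in it. This lowers the likely number of informed recruits but does not make it zero, and the criterion as worded gives no means of finding out.

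Finally, the article is a condensed account, and a screening questionnaire is mentioned but not shown. It might ask about training. The eligibility criteria are listed in full, however, and they are what decides entry.

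**Conclusion.** The point holds as a modest one. The article uses patients' inexperience as one of two grounds for blinding, yet criterion 3 does not clearly deliver that inexperience for people who have studied, observed or trained in the technique, and the posters can reach them. With self-rated primary outcomes this is worth closing.

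It is a plausible and avoidable threat, not a failure shown by the text. The conclusion rests on two readings: that the campus is that of the TCM university, and that some people there have relevant training. The share of such recruits, their ability to identify their arm and the resulting bias are all unknown. A false-positive rate of 7 to 12% might be taken as the size of the problem, but it only restates an assumed 10 to 20% share and an assumed 0.5 SD gap, and should not be quoted as a finding.

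**What to change.** Reword inclusion criterion 3 so that it asks for no previous catgut implantation at acupoints as a patient, and no training in or practice of acupuncture or catgut implantation. Keep the posters and all other recruitment routes. A bar on students or employees of the trial department would not serve, because that department is otorhinolaryngology and the people concerned are elsewhere in the university.

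Recruitment began on June 1, 2012, so some patients may already be enrolled under the present wording. For them, record any such training without reference to treatment arm, and repeat the primary comparison without those who have it, as a sensitivity analysis.

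The cost is one line in the criteria, one item on the case report form and one additional analysis. A few campus volunteers would be lost, and recruitment might be slightly slower.
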